**Sample size**

Based on the published literature,^13,14^ and the results of the pre-test, we estimated that the difference in postoperative pulmonary complications scores between the intervention and control groups would be 0.3, with a standard deviation of 0.45. For postoperative pulmonary complications incidence, we assumed a rate of 60% in the control group and anticipated a 50% relative reduction in the intervention group. Using a two-sided test with a significance level (α) of 0.05 and a power of 80%, the required sample size was calculated separately for each outcome. The sample size estimation based on postoperative pulmonary complications scores resulted in a requirement of 74 patients, whereas the calculation based on postoperative pulmonary complications incidence indicated a requirement of 58 patients. To ensure sufficient statistical power, the larger sample size of 74 was adopted. Accounting for a dropout rate of 5%, the final recruitment target was set at 80 patients.

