**Statistical Analysis**

The baseline characteristics of patients will be summarized and analyzed using descriptive statistical methods. Normality will be assessed using the Kolmogorov-Smirnov test or the Shapiro-Wilk test. Normally distributed continuous variables will be presented as mean ± standard deviation (mean ± SD), whereas non-normally distributed continuous variables will be expressed as median and interquartile range (median [IQR]). Categorical variables will be reported as frequency and percentage (n, %). Group comparisons will be conducted using appropriate statistical methods based on the type of variable. Independent samples t-tests will be used for normally distributed continuous variables, while the Mann-Whitney U test will be applied for non-normally distributed continuous variables. Categorical variables will be compared using the chi-square test or Fisher’s exact test (for expected counts <5). Subgroup analyses were performed according to preoperative subgroup analyses for the PPC severity score, the primary continuous outcome of the study. Patients were stratified according to preoperative serum albumin levels (<35 g/L and 35–40 g/L) on the basis of the clinically relevant thresholds for hypoalbuminemia. Additional age, sex, and surgical type subgroup analyses were performed to evaluate the consistency of the treatment effect across different patient characteristics and procedures. A two-sided P value of less than 0.05 was considered to indicate statistical significance. All the statistical analyses and visualizations were performed using SPSS software version 25.0 (IBM, Armonk, NY, USA), Origin (OriginLab Corporation, Northampton, MA, USA), and GraphPad Prism (GraphPad Software, San Diego, CA, USA).

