For flow cytometry measurements at different time points, Mauchly’s test will be conducted to assess the assumption of sphericity. If the assumption is met, repeated-measures analysis of variance (repeated-measures ANOVA) will be used, followed by Bonferroni post hoc correction for multiple comparisons. If the assumption is violated, Greenhouse-Geisser correction or the Friedman test (for non-normally distributed data) will be applied. Additionally, the correlation between changes in T-cell subset counts and PPC scores will be analyzed using Spearman’s rank correlation test; Pearson’s correlation analysis will be used if the data are normally distributed. All statistical analyses will be conducted using two-sided tests, with a P-value <0.05 considered statistically significant. For multiple comparisons, P-values will be adjusted using Bonferroni correction. Data processing and visualization will be performed using SPSS 26.0 (IBM, Armonk, NY, USA), Origin (OriginLab Corporation, Northampton, MA, USA), GraphPad Prism (GraphPad Software, San Diego, CA, USA), and R 4.4.0.

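### The subgroup analyses are meant to judge consistency of effect, but the only tests named for the score compare two groups and cannot test whether the effect differs between strata

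*Protocol*

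**What the plan says.** All of the subgroup plan is in the protocol's Statistical Analysis section.

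- **Outcome.** The section plans "subgroup analyses for the PPC severity score, the primary continuous outcome of the study".
- **Factors.** Baseline albumin is split in two: "Patients were stratified according to preoperative serum albumin levels (<35 g/L and 35–40 g/L"). Age, sex and surgical type are added. No age cut-off, surgical categories or expected stratum sizes are given.
- **Purpose.** For the added factors it is stated: "Additional age, sex, and surgical type subgroup analyses were performed to evaluate the consistency of the treatment effect across different patient characteristics and procedures".
- **Tests.** The sentence on comparing groups reads: "Independent samples t-tests will be used for normally distributed continuous variables, while the Mann-Whitney U test will be applied for non-normally distributed continuous variables". Chi-square and Fisher tests are named for categorical variables, so they do not bear on the score.
- **Threshold.** Directly after the subgroup sentences comes "A two-sided P value of less than 0.05 was considered to indicate statistical significance".
- **Multiplicity.** The paragraph on flow cytometry says "For multiple comparisons, P-values will be adjusted using Bonferroni correction". Whether this reaches the subgroups is not clear.

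The section names no interaction term and no regression model for the score.

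**The concern.** Consistency is a question about the difference between two treatment effects. A t-test or Mann-Whitney test inside one stratum asks whether the arms differ in that stratum, and a pair of such tests does not compare the strata. With the methods named, the natural output is one P value per stratum.

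At this sample size, a pattern of one significant and one non-significant stratum is common even when the effect is identical in both, because each stratum has only moderate power. A significant result below 35 g/L beside a non-significant one at 35–40 g/L could then be taken as evidence about which patients respond, when stratum size and chance are enough to produce it.

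**Working it through.** **Inputs**

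- Difference in score and SD, from the Sample size section: "would be 0.3, with a standard deviation of 0.45".
- Two-sided alpha 0.05, power 80%, 74 evaluable patients, 80 to be recruited (Sample size); 1:1 allocation (Randomization).
- Assumed, because the protocol gives no figures: two-level factors, the stratum splits shown below, arms balanced within strata, and a normally distributed score. The real score is a 0–5 grade, so the results are approximate.

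**1. The protocol's own figure.** The normal approximation gives 36 per arm, or 72. The exact t-test calculation gives power 79.7% at 36 per arm and 80.8% at 37 per arm, so 37 × 2 = 74, as stated. Then 74/0.95 = 77.9, or 78; the target of 80 covers this. The inputs are therefore read correctly.

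**2. Power within a stratum (N=80, equal strata, 20 per arm in each).** The noncentrality is (0.3/0.45)/√(1/20 + 1/20) = 0.667/0.316 = 2.11, on 38 degrees of freedom with critical value 2.024. Power is 53.8% (normal approximation 55.9%).

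**3. Chance that exactly one stratum has P<0.05, with the same true effect in both.** The formula is pA(1 − pB) + pB(1 − pA).

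| Split (N=80) | Power in each stratum | Exactly one significant |
|---|---|---|
| 50:50 | 53.8%, 53.8% | 49.7% |
| 40:60 | 44.6%, 61.8% | 51.3% |
| 30:70 | 34.6%, 68.8% | 55.8% |
| 20:80 | 23.7%, 74.7% | 63.0% |

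For the equal split: 2 × 0.538 × 0.462 = 0.497. A simulation of 10,000 trials gave 49.9%. With 74 patients and equal strata the result is 50.0%.

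**4. Dependence on the true effect (N=80, equal strata).**

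| True uniform effect | Exactly one significant |
|---|---|
| 0 | 9.5% (2 × 0.05 × 0.95) |
| 0.1 | 19% |
| 0.2 | 40% |
| 0.3 | 50% |
| 0.4 | 34% |
| 0.5 | 13% |

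**5. Four factors.** In the simulation at the planned effect, with four unrelated 50:50 factors, at least one factor showed the mixed pattern in 79.5% of trials.

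**6. The interaction test instead.** Its false-difference rate is 5% per factor by construction (simulated 4.95%). For at least one of four factors it is 1 − 0.95⁴ = 18.5% (simulated 18.5%). With equal strata at N=80, the standard error of the difference between two stratum effects is 0.45 × √(4/20) = 0.201. Power is Φ(0.3/0.201 − 1.96) = 32% for a difference in effects of 0.3, and Φ(0.6/0.201 − 1.96) = 85% for a difference of 0.6.

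**The case against.** The strongest reply is that the protocol never says each stratum will be tested on its own, or that consistency will be judged by setting stratum P values side by side. The sentence naming the two tests concerns group comparisons in general and comes before the subgroup text. Interaction terms and forest plots are often left to a statistical analysis plan, and none is at hand. The protocol does not rule them out.

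The first part of this stands. A reader might infer a written rule of the form significant here, not significant there, but that rule is only implied by the tests named. The second part stands in part. The section goes well beyond outline: it fixes the subgroup outcome, the factors, the albumin cut, the tests and the threshold, and states the aim. The named tests do not answer that aim, so this is a mismatch in what is written and not only a missing detail.

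A second reply is that Bonferroni adjustment may apply. If it reached the subgroup tests, it would limit the chance of any false positive stratum. It would still not compare the strata, because an adjusted P value within a stratum remains a statement about that stratum alone.

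A third reply is that the cut at 35 g/L is prespecified and given a clinical reason. That is correct, and the cut is not an error.

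**Conclusion.** The point holds in a limited form. The protocol sets consistency of effect as the aim of its subgroup analyses, but for the PPC score it names only two-group tests at P<0.05, which do not address that aim.

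If strata are tested separately, about half of two-level factors would show one significant and one non-significant stratum although the effect is the same in both. This rests on a uniform true effect of 0.3 with SD 0.45, about 80 patients and equal strata. More unequal splits raise the figure, to 63% at 20:80.

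A reader might infer that misleading patterns arise half the time whatever the truth. They do not: the rate is 9.5% per factor with no treatment effect, and 13% to 40% at the other effects tried. Nor do the documents support calling the subgroups a leading claim of the trial. They are not among the secondary objectives or endpoints, and the protocol describes the study as a pilot.

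**What to change.** In the Statistical Analysis section, state that:

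- consistency is assessed by the treatment-by-subgroup interaction estimate with its 95% confidence interval, from a regression model for the PPC score;
- stratum estimates are shown with 95% confidence intervals;
- no conclusion is drawn from comparing P values within strata;
- all subgroup results are exploratory.

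The two albumin strata can stay for display. Entering albumin as a continuous variable in the interaction is optional.

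The cost is a few sentences and one added model, which the software already listed can fit. No further patients or data are needed. The drawback is low power: at N=80 with equal strata, a difference in effects of 0.3 would be detected only about 32% of the time. A non-significant interaction must therefore not be reported as proof of consistency, which is why the interval should be given.

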This study aims to evaluate the clinical effects of exogenous albumin infusion compared to 0.9% saline. The primary objective is to assess the efficacy of albumin infusion in reducing the severity and incidence of PPCs. The secondary objectives include evaluating the duration of postoperative invasive mechanical ventilation, the incidence of postoperative acute kidney injury (AKI), the occurrence of postoperative cardiovascular complications, the length of ICU stay, the total length of hospital stay, all-cause postoperative mortality, and changes in T-cell subsets as measured by flow cytometry. By comprehensively analyzing pulmonary, renal, cardiovascular, and hospitalization-related outcomes, this study aims to systematically assess the clinical value of albumin infusion in perioperative management.

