**Blood Sample Collection and Flow Cytometry Analysis**

Arterial blood samples were collected from patients who provided informed consent for blood sampling and flow cytometry analysis at three time points: preoperatively, at the end of surgery, and 24 hours postoperatively. Blood sampling was performed via an arterial catheter, specifically before the infusion of albumin or saline, at the completion of surgery, and 24 hours postoperatively, to analyze the dynamics of Th1, Th17, Treg, γδ1, γδ17, and γδTreg cell populations.

During the experimental process, whole blood samples underwent erythrocyte lysis to remove red blood cells, thereby optimizing leukocyte isolation efficiency and minimizing interference from non-target cells. The isolated leukocytes were then subjected to sequential processing, including cell stimulation, viability staining, surface staining, and intracellular staining, ensuring the precise identification of different T cell subsets. Following staining, the cells were washed twice with PBS to remove unbound antibodies and dyes, and subsequently resuspended in PBS to preserve cell viability and signal stability. Data acquisition was performed using a FACS Fortessa flow cytometer (BD, San Diego, CA, USA) to ensure high-throughput detection accuracy and reproducibility.

The study utilized a comprehensive panel of antibodies targeting T cell subsets and cytokines, including APC-H7-CD3, BV605-CD4, BV421-TCRγδ, APC-IL-17A, BV510-IFN-γ, PE-Foxp3, PE-CY7-TGF-β1, BB700-IL-10, and isotype-matched control IgG. All antibodies were purchased from BD PharMingen or BioLegend (San Diego, CA, USA). The selection of antibodies was based on validated literature evidence to ensure specificity and sensitivity of the experimental results.

Flow cytometry data were analyzed using FlowJo software (BD, San Diego, CA, USA), employing a standardized gating strategy to ensure data accuracy, consistency, and reproducibility. To minimize potential bias during analysis, all flow cytometry data underwent independent quality control by at least two researchers, thereby enhancing scientific rigor and reliability.

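### The methods named for the three-time-point T-cell data drop every patient without all three samples and state no arm term; a mixed model using every sample would avoid both

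*Protocol*

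**What the plan says.** The section on blood sampling and flow cytometry schedules samples "at three time points: preoperatively, at the end of surgery, and 24 hours postoperatively". The route is given for all three: "Blood sampling was performed via an arterial catheter, specifically before the infusion of albumin or saline, at the completion of surgery, and 24 hours postoperatively". No other route is mentioned, and no time of catheter removal is given. Sampling covers only a consenting subset: "Arterial blood samples were collected from patients who provided informed consent for blood sampling and flow cytometry analysis". The size of that subset is not stated.

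The flow cytometry paragraph of Statistical Analysis starts from Mauchly's test and continues: "If the assumption is met, repeated-measures analysis of variance (repeated-measures ANOVA) will be used". The alternative is: "If the assumption is violated, Greenhouse-Geisser correction or the Friedman test (for non-normally distributed data) will be applied". The paragraph names no method that keeps incomplete patients, and it states neither an arm factor nor an arm-by-time term.

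The aims at the end of the Background list "changes in T-cell subsets as measured by flow cytometry" among the secondary objectives. The secondary list under Study Endpoints does not include them.

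**The concern.** Classical repeated-measures ANOVA needs one value per patient at each time point. The Greenhouse-Geisser correction changes the degrees of freedom, not the set of patients. The Friedman test ranks within complete blocks. Under any of the three, one missing sample removes the patient from every time point. The 24-hour sample looks the most exposed, because it needs a patient who is alive with a working arterial catheter a day after surgery. Losing it would discard two valid measurements from a subset of at most 80 patients.

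Two things are at stake. One is precision for the early time points. The other is whether the patients left in each arm are still comparable. A third point follows from the same sentences: the question of interest is whether albumin changes the T-cell course relative to saline, yet the paragraph does not say where that comparison is made.

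**Working it through.** The protocol gives no figure for the flow cytometry data, so there is none to reproduce; its sample size concerns the pulmonary complication endpoints. Inputs from the protocol are three time points, 1:1 allocation and a recruitment target of 80, hence at most 40 sampled per arm. The missing rates below are assumptions. The only loss figure in the document is the 5% dropout under Sample size.

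**Precision.** Let a share q of 24-hour samples be missing at random. Deleting those patients multiplies the variance of the end-of-surgery arm difference by 1/(1 − q) and its standard error by the square root of that. The last column takes an effect with 80% power at 40 per arm, that is (1.96 + 0.84) × √(2/40) = 0.63 SD, and recomputes the power (normal approximation, two-sided 0.05) with k complete patients per arm.

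| q (assumed) | k of 40 per arm | Variance ratio | SE ratio | Power |
|---|---|---|---|---|
| 5% | 38 | 1/0.95 = 1.05 | 1.026 | 78% |
| 10% | 36 | 1/0.90 = 1.11 | 1.054 | 76% |
| 20% | 32 | 1/0.80 = 1.25 | 1.118 | 71% |
| 30% | 28 | 1/0.70 = 1.43 | 1.195 | 65% |

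This loss is avoidable for the pre-infusion and end-of-surgery values, because they exist. At 24 hours the missing values are gone whatever the method. A model can recover only what the earlier samples predict.

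**Bias, no true arm difference.** Large-sample simulation: three values with SD 1 and correlation 0.6. Where loss depends on a T-cell value, its odds rise by a factor exp(1.5) per SD lower value. Complete-case bias in the arm difference, in SD units:

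- Loss unrelated to T-cell values (20% in both arms, or 10% against 30% or 40%): about 0.
- Loss related to T-cell values but equal in both arms (27% each): about 0.
- Loss related to the end-of-surgery value and unequal by arm (17% against 36% to 43%): 0.19 to 0.26 at end of surgery, 0.11 to 0.15 at the other two times, and about 0 in the change from pre-infusion to 24 hours. A likelihood-type estimate from all samples is about 0 at 24 hours.
- Loss related to the unseen 24-hour value and unequal by arm (17% against 35% to 43%): 0.19 to 0.26 at 24 hours and 0.07 to 0.11 in the change to 24 hours. The all-samples estimate at 24 hours keeps 0.11 to 0.16.

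**Bias, true difference 0.50 SD at both post-infusion times.** Correlation 0.5; the odds of loss rise by a factor e per SD of the end-of-surgery value, by one rule for both arms. Because the arms differ, that single rule gives unequal loss: 13% against 19%, 24% against 32%, and 33% against 43% (overall 16%, 28% and 38%). Results in the same order:

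- End-of-surgery difference, complete cases: 0.45, 0.43, 0.42.
- Change from pre-infusion to end of surgery: 0.48, 0.47, 0.46.
- Change from pre-infusion to 24 hours: 0.50 each time.
- End-of-surgery difference, all samples: 0.50 each time.

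With the true difference set to 0, this rule gives bias of about 0 at every time. The largest shift, 0.05 to 0.08 SD, is toward the null. With 40 per arm the standard error is √(2/40) = 0.22 SD, so the shift is roughly a fifth to a third of one standard error.

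**The case against.** A reader might infer that patients who recover quickly have their catheter out before 24 hours, so that the analysis drops the fast recoverers and biases the comparison. The protocol does not support that. It gives no removal time and does not link removal to recovery. Under Standard Care every patient goes intubated to the ICU for continuous monitoring, and a catheter draw is scheduled at 24 hours. Read together, these fit a catheter still in place. Death or a failed assay could also cost a sample, with selection in other directions. Even selective loss gave no bias in the calculations above unless it also differed by arm, and the change to 24 hours was unbiased when loss depended on the end-of-surgery value. This part of the objection stands.

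It can also be said that the missing rates are assumed, that at 5% the cost is trivial, and that missing-data handling usually belongs to a statistical analysis plan, which is not at hand. The first two are right and limit the size of the point. The third does not remove it. The protocol names the tests, and a plan that follows them inherits the deletion of incomplete patients.

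Finally, the general paragraph of Statistical Analysis provides two-group tests that could be applied at single time points, and the ANOVA might be meant to include arm. Neither is stated for the T-cell data. The Friedman test in any case compares times within patients. A mixed model is no complete cure either, as the residual 0.11 to 0.16 SD shows.

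**Conclusion.** The point holds in a limited form. The stated methods, in standard form, discard measured samples from any patient lacking one of three. For the end-of-surgery comparison this raises the variance by about 5% at 5% missing and by 11% to 43% at 10% to 30% missing, if loss is at random. Those rates are assumptions. Bias between arms is a possibility, not a finding: it needs loss that is related to T-cell values and differs by arm, and the documents establish neither. The absence of a stated arm or arm-by-time term can be read directly from the text and does not depend on any missing rate.

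Severity is low. T-cell change is a secondary objective of a pilot trial, measured in a consenting subset. Nothing here touches the severity or incidence of pulmonary complications, and the calculations should not be read as casting doubt on them.

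**What to change.** Replace the repeated-measures ANOVA and Friedman scheme with a likelihood-based linear mixed model for each T-cell subset. Include arm, time and arm-by-time as fixed effects and an unstructured covariance over the three times, on a transformed scale if the data are skewed, and use every sample obtained. Name the arm-by-time contrasts as the comparison of interest. Report the number of samples by arm and time point, with reasons for loss, so that a reader can see whether loss differs between arms. State that the model does not fully correct loss that depends on the unseen 24-hour value.

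The cost is a change of wording, slightly more modelling work and a distributional assumption on the transformed scale. SPSS and R, both already listed for these data, fit the model. No extra patients or samples are needed.

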**Randomization**

All patients who provided written informed consent were randomly assigned (1:1) to either the albumin group or the control group. Patient allocation was determined using a computer-generated randomization list, with the assignment sequence concealed from investigators to prevent selection bias.

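### The flow cytometry rule names no albumin-versus-saline contrast, and its non-normal branch (the Friedman test) cannot contain one

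*Protocol*

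**What the plan says.** The aims paragraph in the Background sets the comparison: "This study aims to evaluate the clinical effects of exogenous albumin infusion compared to 0.9% saline". Among its secondary objectives it lists "changes in T-cell subsets as measured by flow cytometry". Under Randomization, patients "were randomly assigned (1:1) to either the albumin group or the control group", so there are two independent arms.

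Under Blood Sample Collection and Flow Cytometry Analysis, samples are taken "at three time points: preoperatively, at the end of surgery, and 24 hours postoperatively", the first of them before the study infusion. The stated purpose is "to analyze the dynamics of Th1, Th17, Treg, γδ1, γδ17, and γδTreg cell populations", which makes six subsets. Only patients who consented to this sampling contribute, and no number is given.

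The flow cytometry paragraph of Statistical Analysis begins with Mauchly's test of sphericity. If sphericity holds, "repeated-measures analysis of variance (repeated-measures ANOVA) will be used", with Bonferroni post hoc correction. Otherwise: "If the assumption is violated, Greenhouse-Geisser correction or the Friedman test (for non-normally distributed data) will be applied". The paragraph adds a correlation of T-cell change with the pulmonary complication score and promises Bonferroni adjustment for multiple comparisons. It mentions no treatment group.

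The general paragraph before it says that group comparisons follow the type of variable. For skewed data, the "Mann-Whitney U test will be applied for non-normally distributed continuous variables". It does not mention flow cytometry.

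**The concern.** The question is whether albumin changes the T-cell subsets relative to saline. That calls for a contrast between arms in how the subsets move from the pre-infusion sample. The paragraph written for these data tests change over time. Surgery with bypass may itself shift T cells in both arms, so a time effect does not show an albumin effect.

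The two routes differ in how far they can be rescued. Repeated-measures ANOVA can carry a group factor and a group-by-time term, although the protocol names neither. The Friedman test has no place for them. An analyst who follows the specific rule down its non-normal branch ends with a result that does not bear on the objective, and must then choose a between-arm test after seeing the data.

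The trigger is a second flaw. Mauchly's test examines the covariance structure of the repeated measures, yet it controls whether a rank test is considered at all.

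**Working it through.** The protocol gives no sample size or power figure for the T-cell analysis, so there is no stated figure to reproduce. The check is structural.

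**1. What the rule assigns**

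| Sphericity (Mauchly) | Data | Assigned method | Between-arm term |
|---|---|---|---|
| holds | normal | repeated-measures ANOVA | possible, not named |
| holds | non-normal | repeated-measures ANOVA | possible, not named |
| violated | normal | ANOVA with Greenhouse-Geisser | possible, not named |
| violated | non-normal | Friedman | not possible |

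The second row shows the misplaced trigger: non-normal data that pass Mauchly's test stay with ANOVA.

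**2. What Friedman measures**

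With n patients and k times, and R_j the sum over patients of the within-patient rank at time j:

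Q = [12 / (n k (k+1))] × ΣR_j² − 3n(k+1)

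For k = 3 this is Q = (1/n) ΣR_j² − 12n, referred to chi-square with 2 degrees of freedom (5% critical value −2 ln 0.05 = 5.99). Arm does not enter. Two extreme cases need no assumed variances. For illustration take n = 74, the protocol's calculated sample size, as 37 per arm.

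- *Every patient in both arms rises steadily; albumin does nothing.* Ranks are 1, 2, 3 for everyone, so the rank sums are n, 2n, 3n. Q = (1/n)(n² + 4n² + 9n²) − 12n = 14n − 12n = 2n = 148. This is overwhelmingly significant with no difference between arms.
- *Every albumin patient rises and every saline patient falls.* Ranks are 1, 2, 3 in one arm and 3, 2, 1 in the other, so each rank sum is 2n. Q = (1/n)(3 × 4n²) − 12n = 12n − 12n = 0. The largest possible divergence between arms is invisible.
- *Friedman run separately per arm on the second case.* Each arm gives 2 × 37 = 74, significant in both, and still without a comparison.

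**3. Simulation as illustration only**

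The protocol gives no variances, time effects or number sampled, so all inputs here are assumed: log-normal data, three times, two-sided 0.05, and the same shift at both post-infusion samples. Shifts and SDs are on the log scale.

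| Per arm | Patient SD / residual SD | True change | Pooled Friedman significant | Between-arm Mann-Whitney on log change significant |
|---|---|---|---|---|
| 37 | 0.7 / 0.7 | none | 5% | 5% |
| 20 | 1 / 0.5 | +0.25 in both arms | 46% to 49% | not tabulated |
| 38 | 1 / 0.5 | +0.25 in both arms | 78% | 6% |
| 37 | 0.7 / 0.7 | +0.5 in both arms | 97% | 5% |
| 37 | 0.7 / 0.7 | saline −0.35, albumin +0.35 | 4% | 84% |

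In the first four rows albumin has no effect, and Friedman runs from 5% to 97% according to the time effect put in. In the last row albumin has a real effect, and Friedman stays near its nominal level.

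If Friedman were run per arm and the verdicts compared, with no albumin effect, the chance that the arms disagree is 2p(1−p), where p is each arm's rejection probability. This cannot exceed 2 × 0.5 × 0.5 = 50%. With 38 per arm (SDs 1 and 0.5) it was 17%, 48%, 6% and 0% at common shifts of 0.1, 0.25, 0.5 and 0.8.

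**The case against.** **A between-arm test for skewed data is already in the protocol.** The general paragraph gives Mann-Whitney for group comparisons and nothing there excludes flow cytometry. The flow paragraph can be read as adding a time analysis on top. A reader might therefore infer too much in saying that the plan as a whole cannot answer the T-cell question, and the documents do not support that stronger statement. What remains is that the general rule is not linked to these data, to one of the three times or to change from the pre-infusion sample, while the paragraph that does address these data gives a different rule.

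**Skewness alone does not lead to Friedman.** A reader might infer that any skewed subset loses its arm comparison. The text requires sphericity to be violated as well, and otherwise keeps an ANOVA that can hold a group-by-time term. This objection stands. The protocol also gives no evidence on how skewed the subsets will be.

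**The percentages depend on what is put in.** A reader might take the high Friedman rates as false-positive rates for albumin. They are power for a time effect that the simulation inserted. The disagreement rates concern a per-arm practice that the protocol nowhere states. Both objections stand, which is why the argument rests on the algebra.

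**A statistical analysis plan may settle it.** Such a plan could name the contrast. It would, however, have to replace a test the protocol has already fixed, so this is more than detail left for later. Handling of missing samples and use of the pre-infusion value as a covariate are properly left to that plan and form no part of this point.

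**The weight is limited.** T-cell change is in the stated objectives but absent from the secondary endpoint list under Study Endpoints. The sampling section speaks of dynamics, the sample is a consenting subset, and the trial is a pilot. All of this lowers the stakes. It does not remove the objective, which sits inside the albumin-versus-saline comparison.

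**Conclusion.** The point holds in this form: the rule specific to flow cytometry names no between-arm contrast on any branch; on the branch with violated sphericity and non-normal data it names a test that cannot contain one; and it lets Mauchly's test govern a choice that should rest on normality. Followed as written, it does not answer the T-cell objective.

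The conclusion rests on the form of the Friedman statistic and on reading the flow paragraph as the governing rule for these data. It does not depend on any assumed variance, effect or sample size. No single percentage measures the harm: in the scenarios without an albumin effect, Friedman rejected in 5% to 97% of trials depending on the assumed time effect and number sampled.

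The consequence is limited to a secondary, mechanistic objective. The primary analysis of pulmonary complications is unaffected. The change is worth making because it costs little and prevents a time effect from being reported as an albumin effect.

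**What to change.** Rewrite the flow cytometry paragraph so that the between-arm contrast is the stated T-cell analysis.

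- **Main route:** for each subset, the group-by-time term of a mixed ANOVA or mixed model, on transformed values if skewed. Mauchly's test, if kept, decides only whether the Greenhouse-Geisser correction is applied to the ANOVA.
- **Non-normal route:** replace Friedman with Mann-Whitney on change from the pre-infusion sample, or with baseline-adjusted ANCOVA on transformed values. Name the post-infusion time that carries the test.
- **Choice of route:** decide on normality, not on Mauchly's test.
- **Multiplicity:** apply the promised Bonferroni adjustment over the six subsets, 0.05 / 6 = 0.0083 for one contrast per subset. If both post-infusion times are tested, count both.
- **Friedman**, if kept, is labelled as a description of change over time and not as evidence on albumin.

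The cost is wording and minor analysis work. No new data or samples are needed, and SPSS and R are already listed.
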